## Methods

### Study Design and Overview

The study adopts an 8-week, two-arm cluster RCT design that is planned to be conducted during Spring and Summer months (see Figure 1 for overview of study design). The unit of randomization will be the workers' offices in line with previous research (24). Participants will be randomly allocated into clusters with each cluster being in either the control or intervention group for a period of 8 weeks. Given the nature of the intervention, blinding from participants or the core research team is not possible.

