**Figure 1 F1:**
[figure not shown]
Overview of study design.

The study is registered on ClinicalTrials.gov (NCT03560544). Ethical approval for the procedures detailed below was obtained from the University of Bedfordshire Institute for Health Research Ethics Committee (lHREC836). Participants will provide written informed consent prior to any testing procedures and the study is being conducted in accordance with the Declaration of Helsinki.

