### Study Setting

The study will be conducted with office workers employed across a university campus and a local council, both located in the East of England region, UK. Participants were recruited from one campus at the university and employees at the council worked within offices at a single site. Clusters of participants will be recruited from both organizations who will be randomly allocated to the intervention or control group i.e., there will be intervention and control clusters located at each organization.

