### Randomization

To minimize contamination between groups in open plan offices, a cluster randomization approach will be used with offices being the unit of randomization i.e., randomization into either the intervention or control group will be assigned on an office basis (28). The number of clusters is projected to be approximately eight with an average cluster size of six (29). Randomization will be achieved by assigning a cluster ID to each office and clusters then being allocated to intervention or control group using an online randomization tool (https://www.randomlists.com/team-generator) by an independent researcher (30). Randomization will take place before the collection of baseline measurements and group allocation will not be disclosed to participants until the completion of baseline assessment (28).

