###### Fasting Blood Glucose and Lipid Profile.

Blood samples taken after an overnight fast of at least 10 h using a finger prick method with a lancet (52). Blood samples will be analyzed with a Cholestech LDX analyzer (Cholestech Corp., Hayward, CA., USA) to provide measures of total cholesterol, high-density lipoprotein cholesterol, low-density lipoprotein cholesterol, triglycerides and blood glucose (52).

*Blood Pressure*. Resting systolic and diastolic blood pressure will be measured on the right arm after resting for at least 10 min in a seated position using an automated blood pressure monitor (Omron HEM705 CP, Omron Healthcare UK Limited, Milton Keynes, UK) validated by the European Society of Hypertension (53). The average of two blood pressure readings with a 2-min rest between each will be used for analysis.

*Anthropometry*. The standardized procedure of Lohman et al., (54) will be used. Height is measured with a stadiometer (Horltain Ltd., Crymych, UK) to the nearest 0.1 cm, while mass is measured with an electronic weighing scale (Tanita Corp., Tokyo, Japan) to the nearest 0.1 kg. Waist circumference is recorded to the nearest 0.1 cm measured around the waist at navel-level while participants are standing (55, 56). All measures will be taken by the same investigator to avoid inter-investigator variability. Body mass index will be calculated as: weight / height^2^.

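### Offices are randomised before baseline and allocation is withheld from participants only, so staff-dependent baseline values could be taken or processed with the arm known

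*Protocol article*

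**What the plan says.** The Randomization section of the protocol article makes the office the unit: "randomization into either the intervention or control group will be assigned on an office basis". Each office receives a cluster ID, and the IDs are allocated with an online tool "by an independent researcher". The order of events is explicit: "Randomization will take place before the collection of baseline measurements". Concealment is also explicit, but limited to one group of people: "group allocation will not be disclosed to participants until the completion of baseline assessment".

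Study Design and Overview states that, because of what the intervention is, "blinding from participants or the core research team is not possible". On consent, the paragraph after Figure 1 says: "Participants will provide written informed consent prior to any testing procedures". On recruitment, Study Setting says: "Clusters of participants will be recruited from both organizations who will be randomly allocated to the intervention or control group". Statistical Analysis enters each variable's baseline value as a covariate in its linear mixed model.

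**The concern.** The protocol already accepts that knowing the allocation could affect baseline data, because it hides the allocation from participants until baseline is over. It gives the staff who recruit and measure no such protection and no reason for leaving them out. That delivery cannot be blinded does not require the list to exist, or to be known, before baseline.

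Two things are at stake. First, a baseline value is a sound covariate only if its error does not depend on the arm; a value obtained by someone who knows the arm does not have that guarantee. Second, in a cluster trial the people enrolled in each office should be settled before the office's arm is known. If they are not, selection on motivation or on judgement-dependent eligibility can differ between arms, and adjusting for measured baseline does not remove selection on something unmeasured. The Discussion intends the findings to inform a fully powered trial, so a weak sequence could be carried forward.

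**Working it through.** No power or sample-size arithmetic bears on this point. The check is to set the statements side by side, ask which measures are exposed, and trace how an error would travel.

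**1. Who can know the arm at baseline?**
- The list exists before baseline (Randomization).
- It is produced by someone independent, and the section does not say when the core team receives it.
- Participants are kept unaware until baseline ends; nobody else is named.
- The core team is described as impossible to blind (Study Design and Overview).
- Participant Recruitment, Measurements and the outcome sections contain no statement that staff are kept unaware.

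Staff knowledge at baseline is therefore permitted by the text. It is not stated as a fact.

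**2. Which baseline values depend on staff?**

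| Measure | How it is obtained | Staff input |
|---|---|---|
| Workplace sitting (primary) and other activPAL variables | Device worn by participants unaware of their arm | Visual check of wear time against diaries, with manual correction of waking bouts |
| Waist circumference | Measured by hand at the navel | Direct |
| Blood pressure | Automated monitor after seated rest | Conduct of the procedure, not the reading |
| Glucose and lipids | Analyser, finger-prick sample | Conduct of the sampling, not the assay |
| Questionnaires, ecological momentary assessment | Online or on the participant's smartphone | None described |

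For anthropometry the article adds: "All measures will be taken by the same investigator to avoid inter-investigator variability". That controls differences between observers. It does not say that the one observer is unaware of the arm.

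**3. How would a baseline error reach the result?** With the baseline value as covariate, the adjusted difference at follow-up is in essence

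D = (Y_I − Y_C) − β (X_I − X_C),

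where Y and X are arm means at follow-up and baseline (I intervention, C control) and β is the within-arm slope. If knowledge of the arm shifts the recorded X_I − X_C by δ, then D shifts by −βδ. Error common to both arms gives δ = 0 and no such shift. The documents give neither β nor δ, so no figure follows.

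**4. Is enrolment closed before allocation?** Two sequences fit the text:
- recruit, consent, randomise, measure;
- recruit, randomise, consent, measure.

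Study Setting favours recruitment before allocation, because it speaks of clusters of participants being recruited and then allocated. The consent sentence refers to testing, not to randomisation, so the second sequence is not ruled out. Eligibility includes a history of musculoskeletal complaints, which calls for some judgement. The gap is real, but nothing shows that anyone would be enrolled with the arm known.

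**The case against.** The strongest reply has four parts.

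- *The blinding sentence concerns delivery.* It is tied to the nature of the intervention, and desks visibly change only once the intervention starts. It need not mean that the team holds the list during baseline. This stands: staff knowledge at baseline is an inference. It does not close the gap, because the one sentence that sets concealment names participants alone.
- *Recruitment comes first.* A reader might infer that enrolment itself is open to influence by known allocation. The documents do not support that as a finding. Randomisation is placed before baseline measurement, not before recruitment. Study Setting reads as recruitment followed by allocation, and the plan in Table 4 for at least two participants per office fits clusters formed beforehand. Only the possibility remains.
- *The primary outcome is protected.* Sitting is recorded by a device on people who do not know their arm. This largely stands. A reader might want to put a number of minutes on the bias in sitting time, but the documents offer no mechanism for a sizeable differential error there beyond the manual wear-time corrections. Likewise, a shift in an arm's mean baseline sitting caused by selective loss would be largely removed by baseline adjustment, so it is not a measure of bias in the effect.
- *This is a condensed article.* The full protocol may say when consent closes and who sees the list. That is fair for the consent point. It does not answer the main one, since the order of randomisation and baseline, and the limit of concealment to participants, are rules the article states.

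**Conclusion.** The point holds as a weakness in a stated design rule. Randomisation precedes baseline, concealment covers participants only, the core team is declared unblinded, and nothing keeps recruiting or assessing staff unaware. Staff-dependent baseline values that serve as covariates could therefore be obtained or processed with the arm known. The realistic exposure is waist circumference first, then the manual activPAL corrections and the conduct of the blood pressure and finger-prick procedures. Self-completed measures are not exposed by this route.

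The size cannot be calculated from the documents, and none is claimed. The conclusion assumes that the core team, or whoever measures, may receive the list before baseline ends; if the independent researcher in fact holds it until then, the exposure at baseline measurement disappears. Enrolment bias is a possibility left open by the consent wording, not a demonstrated defect. For a pilot with a device-measured primary outcome this does not undermine the trial, but it should be corrected because the better sequence is nearly free.

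**What to change.** Amend the Randomization section so that the independent researcher randomises offices only after consent, eligibility and all baseline measures are complete in every office, or in every office of a recruitment wave. The allocation is released to the core team at that point.

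If logistics need an earlier allocation, keep the present order but state that the independent researcher holds the list from recruiting and assessing staff until baseline is complete. Under either option, say that the baseline activPAL wear-time corrections are finished before release, or are made by someone unaware of the arm; otherwise that processing could still follow disclosure.

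The Abstract describes the study as ongoing. If offices have already been allocated, report the sequence actually followed for consent, allocation and baseline, and who knew the allocation at each step.

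The cost is a few sentences and a short delay between baseline and workstation installation. No extra staff are needed, since the independent researcher is already in the plan. The change does not blind the week 8 assessments.

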### Intervention Development, Content and Delivery

The intervention described in this study protocol was developed by systematically following the BCW framework (20, 31). The first step was to identify the problem (health and cardiovascular disease risk) in behavioral terms (sedentary behavior) and specify the target behavior to be changed (sitting at work). This was then followed by a COM-B (Capability, Opportunity and Motivation-Behavior) behavioral analysis conducted for the identification of barriers and facilitators to breaking up workplace sitting in office workers (32). The analysis led to the identification of seven core themes [“*Knowledge-deficit sitting behavior,” “Willingness to change,” “Inadequate cognitive resources for action,” “Tied to the desk,” “Competing motivations,” “Emotional influences,” and “Organizational support and interpersonal influences”* (32)], which linked to five of the six COM constructs and 12 domains of the Theoretical Domains Framework (TDF) (33). The TDF serves as a theoretical lens for understanding the cognitive, affective, social and environmental influences on behavior (33, 34). Subsequently, seven possible intervention functions, three policy categories and 38 behavior change techniques (BCTs) based on the BCT Taxonomy version 1 (35) that could be considered for inclusion in an intervention for reducing and breaking up workplace sitting were identified (36).

In deciding which intervention functions, policy categories and BCTs were most appropriate or have the highest possibility of success in delivering the desired change in this context, the Acceptability, Practicability, Effectiveness/cost-effectiveness, Affordability, Safety/side-effects, Equity (APEASE) criteria was applied. This is line with recommendations for using the BCW in practice (21, 37). Initial judgments using the APEASE criteria were made by the first author and reviewed by the co-authors ([name]) until consensus regarding acceptance or rejection was reached. This led to identifying for inclusion, five intervention functions (Education, Persuasion, Enablement, Training and Environmental Restructuring; see Table 1), three policy categories (Communication/Marketing, Guidelines, and Environmental/Social Planning; Table 2) and 17 BCTs [*Goal setting (behavior), Action planning, Problem solving, Instruction on how to perform the behavior, Credible source, Information about health consequences, Information about emotional consequences, Prompts/cues, Social support [unspecified], Restructuring the physical environment, Restructuring the social environment, Adding objects to the environment, Behavioral practice/rehearsal, Behavior substitution, Habit formation, Habit reversal and Demonstration of the behavior*; see Table 3]. Table 4 shows a logic model, whereby the intervention content specified by BCTs is mapped onto components of the TDF and COM-B model. It also includes description of the delivery mode for the intervention content. The intervention thus includes a combination of education, persuasion, training, enablement, and environmental restructuring with the aim of addressing all of the identified constructs of the COM-B model and TDF. The intervention strategies and modes of delivery consist of an information session provided by a researcher and a leaflet covering the health consequences of prolonged sitting and the benefits of breaking up sitting, goal setting, action planning; computer prompt software; line manager support; and a height-adjustable workstation at each individual's desk. The computer prompt Google Chrome extension “Marinara: Pomodoro Assistant” will be installed on participant's computers. This prompt software has a customisable timer that can be used to set prompt alerts that appear as pop-up messages on the screen to remind the user to take a break. The break duration is customisable and the user is notified when the break has ended.

**Table 1 T1:** Selection of intervention functions to cause a change in sitting behavior in desk-based employees.

**Intervention function**	**A**	**P**	**E**	**A**	**S**	**E**	**Comments**
Education	✓	✓	✓	✓	✓	✓	Information regarding the consequences of prolonged sitting and why sitting should be interrupted is readily available.
Enablement	✓	✓	✓	✓	✓	✓	Permission that permits participants to break up sitting is already granted by employee's management.
Training	✓	✓	✓	✓	✓	✓	Instruction on how to carry out the proposed sitting behavior will be provided and demonstrated to participants.
Persuasion	✓	✓	✓	✓	✓	✓	Safe resources for the delivery of this function are readily available. For instance, consequences of uninterrupted sitting, information regarding sitting guideline and participants can be supported in setting targets and planning to achieve them.
Incentivisation	✓					✓	No funds available, therefore it is not practicable or affordable. No evidence for effectiveness or side-effects.
Environmental restructuring	✓	✓	✓	✓	✓	✓	Made possible due to equipment donation.
Modeling	✓		✓	✓	✓	✓	Not practicable to identify a timekeeper who could get people moving as participants will be in clusters in different offices.

*(Left to right) A, Acceptability; P, Practicality; E, Effectiveness; A, Affordability; S, Side-effect/safety; E, Equity; ✓, Intervention function meets APEASE criterion*.

**Table 2 T2:** Identification of policy categories to support the intervention delivery.

**Policy categories**	**A**	**P**	**E**	**A**	**S**	**E**	**Comments**
Communication /Marketing	✓	✓	✓	✓	✓	✓	These policies are relevant as there is a need to educate participants about what to do and why change is important.
Guidelines	✓	✓	✓	✓	✓	✓	Although development of new guidelines is not warranted, participants' attention will be drawn to existing guidelines for sitting among office workers.
Environmental/Social Planning	✓	✓	✓	✓	✓	✓	Permission will be obtained from the participating organization management to modify the offices.

*(Left to right) A, Acceptability; P, Practicality; E, Effectiveness; A, Affordability; S, Side-effect/safety; E, Equity; ✓, Policy category meets APEASE criterion*.

**Table 3 T3:** Screening of the possible behavior change techniques (BCTs) with APEASE criteria.

**BCT (code) [Obtained from a preceding qualitative study (32)]**	**A**	**P**	**E**	**A**	**S**	**E**	**Comments**
Goal setting (behavior) (1.1)	✓	✓	✓	✓	✓	✓	
Problem solving (1.2)	✓	✓	✓	✓	✓	✓	
Action planning (1.4)	✓	✓	✓	✓	✓	✓	
Monitoring of behavior by others without feedback (2.1)	✓		✓	✓	✓	✓	Not practicable as colleagues will not have time.
Feedback on behavior (2.2)	✓		✓		✓	✓	Not affordable and practicable in this context, as a monitoring device needs be worn then retrieved before feedback can be provided.
Self-monitoring of behavior (2.3)	✓	✓	✓		✓	✓	Not affordable in this context as a monitoring device will need to be provided for and worn by all the participants.
Self-monitoring of outcome(s) of behavior (2.4)	✓		✓	✓	✓	✓	The intervention will be short-term. Therefore, it may be difficult and not practicable to measure and observe any noticeable change.
Social support (unspecified) (3.1)	✓	✓	✓	✓	✓	✓	
Social support (practical) (3.2)			✓	✓	✓	✓	Practical help from other colleagues does not appear acceptable or practical due to limited time and competing priorities of colleagues.
Instruction on how to perform the behavior (4.1)	✓	✓	✓	✓	✓	✓	
Information about Antecedents (4.2)	✓		✓	✓	✓	✓	Participants might feel overburdened by needing to record events taking place around sitting periods.
Behavioral experiments (4.4)	✓			✓	✓	✓	Although advice regarding consequences of prolonged siting behavior will be provided based on existing evidence, it will be difficult in terms of cost-effectiveness and practicality to collect data to advise the participants prior to the intervention.
Information about health consequences (5.1)	✓	✓	✓	✓	✓	✓	
Information about social and environmental consequences (5.3)	✓			✓	✓	✓	Not practicable as information is not known.
Information about emotional consequences (5.6)	✓	✓	✓	✓	✓	✓	
Demonstration of the behavior (6.1)	✓	✓	✓	✓	✓	✓	
Social comparison (6.2)		✓	✓	✓		✓	Revealing information about others' sitting time would breach confidentiality, which may be deemed unacceptable. Comparing to others may make others feel uncomfortable as a side effect.
Information about others' approval (6.3)	✓			✓	✓	✓	Not practicable as it is difficult to know what others think about sitting behavior in the workplace.
Prompts/cues (7.1)	✓	✓	✓	✓	✓	✓	
Behavioral practice/rehearsal (8.1)	✓	✓	✓	✓	✓	✓	
Behavior substitution (8.2)	✓	✓	✓	✓	✓	✓	
Habit formation (8.3)	✓	✓	✓	✓	✓	✓	
Habit reversal (8.4)	✓	✓	✓	✓	✓	✓	
Credible source (9.1)	✓	✓	✓	✓	✓	✓	
Material incentive (behavior) (10.1)	✓		✓		✓	✓	Not practicable, affordable or sustainable in this context.
Material reward (behavior) (10.2)	✓		✓		✓	✓	Not practicable, affordable or sustainable in this context.
Non-specific reward (10.3)	✓		✓		✓	✓	Not practicable, affordable or sustainable in this context.
Social reward (10.4)	✓		✓	✓	✓	✓	Not practicable (time consuming).
Social incentive (10.5)	✓		✓	✓	✓	✓	Not practicable (time consuming).
Non-specific incentive (10.6)	✓		✓		✓	✓	Not practicable, affordable or sustainable in this context.
Incentive (outcome) (10.8)	✓		✓		✓	✓	Not practicable, affordable or sustainable in this context.
Self-reward (10.9)	✓		✓		✓	✓	Not practicable or affordable as participants may not have time or ability to self-praise or have money to buy themselves gifts as a reward for breaking up sitting.
Reduce negative emotions (11.2)	✓		✓	✓	✓	✓	Not practicable as would require time and support from others to provide personalized advice.
Restructuring the physical environment (12.1)	✓	✓	✓	✓	✓	✓	
Restructuring the social environment (12.2)	✓	✓	✓	✓	✓	✓	
Adding object to the environment (12.5)	✓	✓	✓	✓	✓	✓	
Verbal persuasion about capability (15.1)	✓		✓	✓	✓	✓	Participants do not need any special skill to break up their sitting, however, there may be unseen physical limitations. So as not to pry into participants' privacy, it is considered not practicable.
Mental rehearsal of successful performance (15.2)	✓				✓	✓	Not practicable as it is difficult to ascertain if participants will have time to start imagining their ability to break up sitting while at work. It might be seen as a distraction and hence cannot be said to be practical and/or affordable. There is no data to confirm whether it could be effective.

*(Left to Right) A, Acceptability; P, Practicality; E, Effectiveness; A, Affordability; S, Side-effect/safety; E, Equity; ✓, BCT meets APEASE criterion*.

**Table 4 T4:** Intervention content specified by behavior change techniques mapped onto components of TDF and COM-B model.

**Behavior change techniques**	**BCT definition (35)**	**COM-B construct targeted**	**TDF-domain targeted**	**Intervention function**	**Policy category**	**Intervention content and mode of delivery**
1.1 Goal setting (behavior)	Set or agree on a goal defined in terms of the behavior to be achieved	Reflective motivation	Goals	Enablement	Communication/Marketing	Participants will be advised and supported face-to-face to set bi-weekly goals for the duration of time spent sitting. This means that they will set different target for weeks 2, 4 and 6 to achieve both the minimum (2 h) and maximum (4 h) time for standing at work as advised in an expert statement (12).
1.2 Problem solving	Analyse, or prompt the person to analyse, factors influencing the behavior and generate or select strategies that include overcoming barriers and/or increasing facilitators	Psychological capability; Reflective motivation	Behavioral regulation; Goals	Enablement	Communication/Marketing	Ideas for problem solving will be provided in an information leaflet and within emails sent by managers providing support for engaging in the intervention. The research team will support participants in developing an action plan in relation to how they will break up their sitting to achieve sitting/standing targets (e.g., to stand every 30 min during the working day) and how to manage this around competing work duties. This will include how they will use computer prompt software to support the behavior. Computer prompt software will be installed on participants' computers to support frequent alternations in posture in addition to bi-weekly emails from line managers to encourage participants to work toward their targets.
1.4 Action planning	Prompt detailed planning of performance of the behavior (must include at least one of context, frequency, duration and intensity).					
3.1 Social support (unspecified)	Advise on, arrange or provide social support (e.g., from friends, relatives, colleagues, buddies or staff) or non-contingent praise or reward for performance of the behavior	Social opportunity; Physical opportunity; Reflective motivation	Social influences; Environmental context and resources; Social/Professional role and identity	Enablement; Environmental restructuring	Environmental/Social planning;	Approval will be sought and obtained from participating organization management. Participants will be assured via email from managers that they will not be penalized by participating in the study. Line managers will send bi-weekly emails that contain tips for breaking up sitting, appreciating commitment of the participants working toward breaking up prolonged sitting and reminding them of their bi-weekly goals in weeks 2, 4 and 6 (24). The programme will be designed in such a way that at least two people from the same office will participate in the intervention. This will provide the participants the opportunity to support one another and reduce the feeling of aloneness or being judged.
4.1 Instruction on how to perform the behavior	Advise or agree on how to perform the behavior (includes “Skills training”) Note: when the person attends classes	Psychological capability	Skills; Knowledge	Training; Education	Guidelines	A face-to-face training session will be provided to the participants by one member of the research team on how to break up sitting using prompt software and a height-adjustable workstation. Definition of prolonged sitting (sitting > 30 min) will be provided and participants will be advised to not sit more than 30 min in one continuous bout (28, 38). Participants will be provided with a leaflet containing information on the recommended sitting time guidelines, which states that office workers should be on their feet at work, for a minimum of 2 h initially and progressively increase to 4 h per day.
5.1 Information about health consequences	Provide information (e.g., written, verbal, visual) about health consequences of performing the behavior	Psychological capability; Reflective motivation	Knowledge; Belief about consequences	Education; Persuasion	Communication/Marketing; Guidelines	A face-to-face information session will be organized, and participants will be educated about information regarding the health consequences of prolonged sitting and the benefits of breaking up sitting. A leaflet containing the information will also be provided.
5.6 Information about emotional consequences	Provide information (e.g., written, verbal, visual) about emotional consequences of performing the behavior	Psychological capability; Reflective motivation	Knowledge; Belief about consequences	Education; Persuasion	Communication/Marketing	Verbal information regarding some of the emotional consequences (such as anxiety and depression) of prolonged sitting will be provided during a 10-min information session.
6.1 Demonstration of the behavior	Provide an observable sample of the performance of the behavior, directly in person or indirectly	Psychological capability	Skills; Knowledge	Training; Education; Modeling; Persuasion	Guidelines, Communication/Marketing	A step-by-step guide on how the intervention is being delivered will be provided to participants in a leaflet and a demonstration of intervention components will be delivered to participants (27).
7.1 Prompts/cues	Introduce or define environmental or social stimulus with the purpose of prompting or cueing the behavior.	Physical opportunity; Psychological capability	Environmental context and resources; Memory, attention and decision processes	Environmental restructuring; Enablement	Environmental/Social planning	Prompt software will be installed on participants' computers. This software will be used to provide reminders to change between sitting and standing, and to remind participants to take short breaks (e.g., walking) based on participant preference.
8.1 Behavioral practice/rehearsal	Prompt practice or rehearsal of the performance of the behavior one or more times in a context or at a time when the performance may not be necessary, in order to increase habit and skill	Physical opportunity	Environmental context and resources; Skills	Environmental restructuring; Training	Environmental/Social planning	A Work-Fit-T Sit-Stand Desktop Workstation (Ergotron, St Paul, MN, USA) will be installed at participants' regular desks. This will provide them with the opportunity to alternate between sitting and standing while working.
8.2 Behavior substitution	Prompt substitution of the unwanted behavior with a wanted or neutral behavior	Physical opportunity; Psychological capability	Environmental context and resources; Memory, attention and decision processes	Environmental restructuring; Enablement	Environmental/Social planning	Installation of a Work-Fit-T Sit-Stand Desktop Workstation (Ergotron, St Paul, MN, USA) and prompt software on participant's computers will be used to provide reminders for participants to alternate between standing and sitting and form new habits around sitting less. Participants will be encouraged within the information leaflet and meeting with a researcher to intermittently substitute sitting with standing work
8.3 Habit formation	Prompt rehearsal and repetition of the behavior in the same context repeatedly so that the context elicits the behavior					
8.4 Habit reversal	Prompt rehearsal and repetition of an alternative behavior to replace an unwanted habitual behavior					
9.1 Credible source	Present verbal or visual communication from a credible source in favor of or against the behavior	Psychological capability; Reflective motivation	Knowledge; Beliefs about consequences	Education; Persuasion	Communication/Marketing	A verbal communication based on an expert statement (12) about the need for office workers to reduce sitting and how this could be achieved will be provided by the researchers. The information will also be available in a leaflet.
12.1 Restructuring the physical environment	Change, or advise to change the physical environment in order to facilitate performance of the wanted behavior or create barriers to the unwanted behavior	Physical opportunity	Environmental context and resources	Environmental restructuring	Environmental/Social planning	Height-adjustable workstations will be installed on participant's regular desks to afford them the opportunity to alternate between sitting and standing while working.
12.5 Adding object to the environment	Add objects to the environment in order to facilitate performance of the behavior					
12.2 Restructuring the social environment	Change, or advise to change the social environment in order to facilitate performance of the wanted behavior or create barriers to the unwanted behaviur (other than prompts/cues, rewards and punishments)	Social opportunity	Social influences; Environmental context and resources	Enablement; Environmental restructuring	Environmental/Social planning	Intervention participants will be cluster randomized so that others in their office are taking part, which will help prevent feelings of being isolated or criticized and promote peer support.

*TDF, Transtheoretical Domains Framework; COM-B, Capability Opportunity and Motivation-Behavior; BCT, behavior change technique*.

